**Study Protocol**

**Effects of a music–visual guided physical activity promotion program among adults with intellectual disability living in residential care facilities: A cluster-randomized controlled trial**

|  | Justification for conducting the project: | |
| --- | --- | --- |
|  |  | Health needs of the local community (supported by published data or relevant experiences) |
|  |  | The increased life expectancy of individuals with intellectual disability (ID) is accompanied with rising incidence of early onset age-related health problems. A local study revealed that adults with ID living in residential care facilities are at higher risk of cardiometabolic disease and earlier onset of dementia upon the age of 40 when compared to general population^1^. ID is defined as a significant limitation of intellectual functioning and adaptive behaviour, including practical and social skills, and with onset before the age of 18; its prevalence in Hong Kong is 1.4%^2^. The twofold increased risk entails a high-expense healthcare (>USD$ 4600 per user) due to high morbidity rates caused by non-communicable diseases among adults with ID at younger age^3^.Thus, a health promotion strategy is urgently needed in this specific population.  Apart from the genetic determinants and the influence of psychotropic medication on health, many of the health issues faced by adults with ID are related to inadequate physical activity (PA)^4^. Substantial evidence showed that adequate PA for adults with ID could improve their physical fitness, prevent cardiometabolic and mental diseases, and reduce the risk of dementia by 18%^5,6^. However, promoting adequate PA (≥150-min moderate-intensity or 75-min vigorous-intensity PA/week) to this population (US Department of Health and Human Service) is a major challenge worldwide, and Hong Kong is no exception. Adults with ID have higher prevalence of being physically inactive (73%)^7^ than the general population (50%)^8^. The situation is much worse among adults with ID living in residential care facilitates compared to those living with families^7^. A local study showed that adults with ID in residential care facilities only engaged 2% of daily time (10 min) in moderate-to-vigorous PA as measured by activity trackers^9^.  Most adults with ID tend to avoid PA^10^. Multi-morbidity, cognitive and behavioural impairments are the common intrinsic PA barriers of this population. Moreover, adults with ID also face external PA barriers, such as lack of access to exercise facilities, finances and support from staff of residential care facilities^11^. Given that one tenth of adults with ID live in 127 residential care facilities in Hong Kong, an appropriate and acceptable PA promotion intervention must be developed for this population experiencing health disparities. |
|  |  | Literature review on others’ strategies to address these needs |
|  |  | Even though the health benefits of PA have been widely studied^6^, only a few studies have investigated the initiation and maintenance of PA among adults with ID. A recent systematic review on PA promotion program for adults with ID showed that group-based PA education with participation could only improve the self-reported weekly PA level in the short term^12^. Another systematic review showed that lifestyle intervention for adults with ID tend to adopt certain behavioural change techniques, such as providing information, planning social support (which helps them achieve a certain behaviour), providing instructions on how to perform a certain behaviour, and setting goal^13^. However, in most PA interventional studies on adults with ID, the selection of these techniques is not theory driven^13^.  In addition, the unsustainable effects of a PA program can also be attributed to the limited environmental facilitator, that is, residential facilities have limited organizational capacity to promote PA of adults with ID^4^. The limited resources, time and knowledge of the staff hinder the promotion of health of adults with ID^4^. Therefore, behavioural change must be achieved at both the organizational and individual levels. |
|  |  | Scientific evidence supporting the strategies to address these needs proposed in this project |
|  | Basing on the health belief model and theory of planned behaviour, the information–motivation–strategy (IMS) model posits that the initiation and maintenance of PA among adults with ID are determined by three elements, **information** (understand what they are supposed to do for adequate PA), **motivation** to perform PA, and practical and appropriate **strategy** to maintain adequate PA^14^. In terms of motivation, the belief of being capable of performing PA (self-efficacy), as well as the social support from staff and others on PA participation are important for adults with ID^10^. A local study of adults with ID showed that exercise self-efficacy is significantly associated with PA level (r=0.44, p <0.05)^15^. The propositions of the IMS model are also consistent with the findings on the facilitator of PA among adults with ID. Specifically, personal facilitators include social interaction with peers, encouragements contingent on efforts and/or progress towards behaviour and praises/reward contingent on successful behaviour^13^, whereas environmental facilitators include fun components and regular nature of PA, as well as staff interest in PA^10^.  Music induces interest and enjoyment. Previous studies showed that PA with music increases the motivation and fun, and reduce the perceived discomfort of PA, resulting in a high PA completion rate (90%) and significant improvement in exercise capacity among adults with ID^16,17^. The rhythmical elements, melodic and harmonic aspects, cultural impact and the extra-musical association of music are the four factors of the motivational qualities of music in the PA context, in which the rhythm response is the most important^18^. The rhythm response refers to an innate human predisposition to synchronize movement with musical rhythms. Apart from serving as an information and motivation of PA, the music tempo is also a practical strategy for both adults with ID and the staff of residential care facilities to achieve moderate-intensity PA. The enhanced music tempo can be an audio reinforcement on the required pace of moderate-intensity PA, which is an important modality to maintain the compliance to PA among adults with ID^19^. We have conducted a four-week group-based music–visual guided PA (MVgPA) for adults with ID living in two hostels of the Hong Chi Association (n = 38) and found a high completion rate (90%) among the participants, a significant increase (15.5%) in PA enjoyment and a significant improvement in their functional exercise capacity as measured by six-minute walk test (23.6±40.9m, p<0.01). The staff of these facilities also reported that the MVgPA can be easily incorporated into the routine of their hostels and they will continue to implement this MVgPA. They were pleased with the improvement shown by their service users after the implementation of such intervention, thereby motivating them to promote PA in the facilities^5^.  PA offers cardiometabolic and psychological benefits to adults with ID. However, its initiation and maintenance pose considerable challenges to healthcare and social workers who support this vulnerable group. Facing the challenges of rising morbidity rates caused by non-communicable diseases among adults with ID at younger age, a timely development of an effective and sustainable strategy based on the IMS model is needed to enhance the PA level, PA self-efficacy and interest, and functional exercise capacity of adults with ID. | |
|  | Aim and Objectives: | |
|  | This project aims to develop a MVgPA intervention based on the IMS model to promote PA among adults with ID who are living in residential care facilities. The specific objectives of this project are to (1) evaluate the effectiveness of this intervention in improving the PA level of these adults, enhancing their self-efficacy and interest in performing PA and improving their functional exercise capacity by conducting a cluster-randomized controlled trial, and (2) examine the acceptability of this intervention among the participants and the staff of residential care facilities. | |
|  | Project Plan: | |
|  | (i) | Target group |
|  |  | ***Participant recruitment***  The person-in-charge of residential care facilities and the non-governmental organizations that serve adults with ID, including the Hong Chi Association who had collaborated with us in our pilot project, will be approached by the research team to seek their collaboration and support in recruiting participants and implementing the project. The research team will organize promotion talks and distribute promotion leaflets of the project to potential participants and their families or guardians. To ensure safety of the participants, PA pre-participation health screening will be performed in accordance with the guidelines of American College Sport Medicine (ACSM, Appendix 1). Medical clearance/approval to participate MVgPA will be sought if they have known cardiovascular, metabolic and/or renal disease, or signs and symptoms suggesting these diseases (as detailed in Appendix 1). An information sheet related to the MVgPA, including the heart rates during the PA and type of exercise, will be provided to the physicians. The eligibility of the participants will be screened based on the following criteria:  *Inclusion criteria:*   1. Chinese adults who are aged 18 years to 64 years and are diagnosed with mild or moderate ID based on the information provided by the residential care facilities; 2. Able to understand basic information and instructions of the intervention and to make decisions upon their participation; 3. Classified as physically inactive (i.e., <150-min moderate-intensity or 75-min vigorous-intensity PA/week, see Appendix 1); 4. Currently using residential service user as stated in the Social Welfare Department (https://www.swd.gov.hk/en/index/site_pubsvc/page_rehab/sub_listofserv/id_sermentalhandi/).   *Exclusion criteria:*   1. Currently enrolled in a regular exercise program; 2. Physically unable to participate in the MVgPA, such as having significant mobility problem; 3. Participation to MVgPA will put them at physiological risk; or 4. At risk of self-harm as determined by the staff of the residential care facilities.   ***Sample size calculation***  A similar study for adults with ID in community residences showed an effect size of 0.41 on PA level change^20^. Assuming a similar effect size on PA level change in our proposed trial, a sample size of 119 participants per each of the control and intervention groups will provide the study with 80% power at 2-sided 5% level of significance, as estimated using the power analysis software PASS 13.0 (NCSS, Kaysville, USA). Furthermore, to account for potential reduction in statistical efficiency due to randomization by residential care facilities (clusters) instead of individual participants, a variance inflation factor, called design effect, will be applied to impose to the estimated sample size. The design effect is given by 1 + (m–1)*ICC, where m=average cluster size and ICC=intracluster correlation coefficient of the underlying outcome. We anticipate that the outcomes of the participants recruited from the same residential care facility are unlikely correlated with one another, particularly for the PA outcome. In this regard, the ICC would be small. A synthesis study revealed that ICC tends to be small in primary care research with a median of 0.005 and inter-quartile range of 0.000 to 0.021^21^. Allowing for a conservative ICC of 0.01 and up to 20% attrition rate in our proposed study, at least 17 participants per each of the 14 residential care facility are therefore required.  ***Cluster randomization***  Randomization will be performed at the cluster level (residential care facility) instead of individual participants to avoid contamination between the intervention and control groups. Baseline data for all participants in each cluster will be completed before randomization. The facilities will be randomized to either intervention or control group in a 1:1 ratio. Eligible participants recruited from the same facility will be allocated to either intervention or control groups accordingly. Group allocation will be concealed from outcome assessors and made according to the random group allocation sequence generated by an independent statistician and the sequence of entry into the study. |

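### The assumed ICC of 0.01 is called conservative though it is under half the upper quartile quoted beside it, and 14 facilities of 17 deliver about 76% power at that ICC and 71% at 0.021, not 80%

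*Protocol*

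**What the plan says.** All of the following is in the Protocol, Project Plan (i) Target group, under Sample size calculation, unless noted.

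- Effect size: an earlier study "showed an effect size of 0.41 on PA level change".
- Size before clustering: "a sample size of 119 participants per each of the control and intervention groups", said to give 80% power with a two-sided 5% test.
- Clustering: the design effect is 1 + (m − 1) × ICC, with m the average cluster size.
- Source for the ICC: "ICC tends to be small in primary care research with a median of 0.005 and inter-quartile range of 0.000 to 0.021".
- Reason for expecting a small ICC: "the outcomes of the participants recruited from the same residential care facility are unlikely correlated with one another", most of all for physical activity (PA).
- Value adopted: "Allowing for a conservative ICC of 0.01 and up to 20% attrition rate", leading to at least 17 participants in each of 14 facilities.
- Allocation (Cluster randomization): "The facilities will be randomized to either intervention or control group in a 1:1 ratio", hence 7 facilities per arm.

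Other sections treat the facility as a determinant of PA. The literature review says that "residential facilities have limited organizational capacity to promote PA of adults with ID" and that change is needed at the organisational as well as the individual level. The section on supporting evidence lists staff interest as an environmental facilitator. Section (iv), Cross-sector collaboration, gives organisational capacity an important role. Section (ii), Implementation plan, has sessions run within the facility in groups of 10 to 12, most of them led by facility staff alone. It also says that twenty participants will be recruited in each intervention facility.

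**The concern.** Calling an ICC conservative tells the reader that the clustering loss has been put at the pessimistic end. Here the quoted inter-quartile range shows otherwise: about a quarter of the source's ICCs are 0.021 or more. That source is described only as primary care research, and the protocol gives no ICC for PA or for residential care.

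The supporting argument is also hard to square with the rest of the document. If staff knowledge, staff interest and organisational capacity affect residents' PA, and if they differ between facilities, residents of one facility will resemble each other on PA. Differences in how staff deliver the sessions would add to this in the intervention arm.

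At stake is the stated power for the primary outcome. Readers are told that 80% has been secured with a margin for clustering.

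**Working it through.** **Inputs.** From the sample size paragraph: standardised difference d = 0.41, two-sided 5%, 80% power, attrition 20%, ICC 0.01, quoted upper quartile 0.021, 14 facilities, 17 per facility. From the 1:1 allocation: 7 facilities per arm.

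**Step 1: reproduce the plan's figure.** A two-sample t-test with d = 0.41 needs 94.35, so 95 per arm.
- 95 / 0.8 = 118.75, so 119 per arm. The stated 119 therefore already contains the attrition. Taken as the number analysed, 119 would give 88% power, not 80%.
- 119 / 7 = 17 per facility.

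So 17 follows from 95 and 20% attrition with a design effect of 1, that is, ICC = 0. I could not reach 17 with any ICC above zero.

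**Step 2: apply the protocol's own design effect.** With m = 17 and ICC 0.01, DE = 1 + 16 × 0.01 = 1.16. Then 95 × 1.16 / 0.8 = 137.75, so 138 per arm, and 138 / 7 = 19.7, so 20 per facility. Solving for m on the participants analysed gives 19.4, again 20.

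**Step 3: power of 14 × 17.** After 20% attrition, 17 × 0.8 = 13.6 are analysed per facility and 7 × 13.6 = 95.2 per arm.
- DE = 1 + 12.6 × ICC
- n_eff = 95.2 / DE
- Power = Φ(0.41 × √(n_eff / 2) − 1.96)

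For example, at ICC 0.01: 0.41 × √(84.5 / 2) − 1.96 = 0.705, and Φ(0.705) = 0.76. The last column uses a noncentral t with 14 − 2 = 12 degrees of freedom.

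| ICC | DE | n_eff per arm | Power, normal | Power, t on 12 df |
|---|---|---|---|---|
| 0 | 1.000 | 95.2 | 81% | 74% |
| 0.01 | 1.126 | 84.5 | 76% | 69% |
| 0.021 | 1.265 | 75.3 | 71% | 64% |

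**Step 4: separate the causes (normal approximation).** From 81% to 76% is the omitted design effect at the protocol's own ICC. From 76% to 71% is the choice of 0.01 rather than 0.021. The further fall of about 7 points in the last column comes from having few clusters and has nothing to do with the ICC.

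**Step 5: if 20 were recruited in every facility.** Then 16 are analysed per facility and 112 per arm.
- ICC 0.01: DE = 1 + 15 × 0.01 = 1.15, n_eff = 97.4, power 82% (75% on 12 df).
- ICC 0.021: DE = 1.315, n_eff = 85.2, power 76% (69% on 12 df).

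**Step 6: size needed for 80% at 0.021.** With m = 17, DE = 1.336 and 95 × 1.336 / 0.8 = 158.65, so 159 per arm or 23 per facility. Solved on the participants analysed, it is 23.2, so 24. That is 322 to 336 in total against 14 × 17 = 238.

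**The case against.** The case for the sponsor is considerable.

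- 0.01 is twice the quoted median, so it is cautious relative to the centre of the source. This stands. It does not make 0.01 conservative when the next figure in the same sentence is 0.021.
- The documents give no ICC for this outcome in this setting. This also stands. A reader might infer that the true ICC is well above 0.01 and that power is far lower. For instance, an assumed 0.05 would give about 60% (53% on 12 df). Nothing in the documents supports 0.05 or any other particular value.
- A reader might see an outright contradiction between the small-ICC rationale and the trial's premise. That goes too far. A limit on capacity common to all facilities creates no variance between them. Group sessions take place in the intervention arm only, while PA is measured one week and three months after the intervention. The calculation concerns change in PA, whose ICC may be lower than that of its level, although the protocol does not argue this. What remains is tension: the protocol's account makes some within-facility correlation plausible, and the sentence waves it away.
- A reader might blame the whole shortfall on the ICC. Steps 1 and 4 show that this is wrong. No ICC entered the figure of 17, so changing its value alone would alter nothing.
- The implementation plan's twenty per intervention facility would restore 80% at ICC 0.01 if it applied to every facility. The document states it for one arm only, and the sample size paragraph says at least 17 for all 14.

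**Conclusion.** The point holds in a limited form. The word conservative is not justified by the source quoted for it, and the rationale for near-zero correlation sits badly with the protocol's own account of what drives PA. The stated 80% is not delivered by 14 × 17: power is about 76% at ICC 0.01 and 71% at 0.021. About 5 points are lost to the omitted design effect and about 5 more if the ICC is 0.021.

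These figures assume d = 0.41, 20% attrition spread evenly, equal facility sizes and a normal approximation. With t on 12 df they are 69% and 64%, a separate effect of having only 14 clusters. That 0.01 is too low for this trial is plausible but not shown, and 0.021 serves here as a sensitivity value taken from the protocol itself.

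**What to change.** In the sample size paragraph:

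1. Delete the word conservative and the sentence saying that outcomes within a facility are unlikely to be correlated. Describe 0.01 as a value between the median and the upper quartile of the quoted source.
2. Apply the design effect, and say that 119 per arm already includes attrition.
3. Restate the delivered power for the planned size at ICC 0.01 and 0.021. Any higher value, such as 0.05, should be labelled as an assumption.
4. Reconcile 17 per facility with the twenty per intervention facility in the implementation plan, and base the power statement on the number that holds. At 17 throughout it is about 76% and 71%; at 20 throughout, about 82% and 76% (normal approximation).

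The cost is rewording and a less favourable stated power. Keeping 80% at 0.021 with 14 facilities would take 23 to 24 participants per facility, which is a substantial enlargement and not part of this fix.

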|  | (iii) | Contingency / alternative plan if any problem encountered during implementation |
|  |  | The major problem that may be encountered in the project implementation is the difficulty in recruiting a sufficient number of adults with ID to achieve the targeted sample size. In addition to the collaboration formed in our previous projects, we will continue seeking collaborations from different non-government organizations. Currently, our team has established collaboration with several non-government organizations, including Hon Chi Association, HK Lutheran Social Service, Fu Hong Society and Po Leung Kuk, for the project implementation. The collaborating residential care facilities have agreed to support in participant recruitment and project implementation as stated in the letter of collaboration. In addition, the participants will receive a supermarket coupon (HK$ 50) as compensation for their participation in each phase of the project to enhance the response and intervention completion rate, as well as the completions of follow-ups.  Stepping is a relatively safe PA. A cue card will be provided to the staff of residential care facilities to remind them to seek immediate medical assistance if their service users experience health/medical emergencies during the project implementation. |
|  | (iv) | Cross-sector collaboration |
|  |  | As mentioned before, the organizational capacity of the residential facilities plays an important role in promoting PA of adults with ID^4^. Apart from providing support on participant recruitment and venue for MVgPA, the residential service providers will be asked during the preparation of interventional material about their opinions on the selection guide and the program itself. This project also aims to enhance the knowledge and skill of the staff about PA promotion by supporting them to act as facilitators of the program and by incorporating the intervention into their daily activities. |
|  | (v) | Indicators and targets |
|  |  | The reach-effectiveness-adoption-implementation-maintenance (RE-AIM) framework will be used to evaluate the acceptability and effectiveness of the intervention.  ***Reach*** will be measured by the proportion of eligible adults with ID who have received and completed the intervention relative to the number of adults with ID who have been approached to participate in the program, which will be recorded during the project.  ***Effectiveness*** will be measured by determining whether the following are observed among participants in the intervention group, compared to those in the control, after the intervention:   - a greater increment of at least 0.35 standardized mean difference (SMD) in mean PA level as measured by their time spent in moderate-to-vigorous PA on the basis of empirical evidence^22^; - a greater increment of at least 0.5 SMD in mean level of PA self-efficacy and interest; and - a greater increment of at least 0.5 SMD in mean functional exercise capacity as measured by conducting a 6MWT.   A 0.5 SMD is equivalent to a medium effect size and is conventionally accepted as clinically relevant difference. The satisfaction level of the participants and the staff will also be determined to assess the acceptability of the intervention.  ***Adoption*** will be measured by the proportion of potential residential care facilities that agreed to promote and implement our intervention relative to all facilities that have been approached, which will be recorded during the project.  ***Implementation*** will be measured by the number of intervention sessions that have been delivered at the residential care facility and the number of participants in each session. Attendance will be taken at each intervention session held at each residential care facility.  ***Maintenance*** will be measured by the proportion of residential care facilities allocated to intervention group that have expressed their willingness to continue implementing the intervention at their centres at post-intervention and the number of MVgPA sessions conducted in a 3-month follow-up period. |
|  | (vi) | Evaluation plan |
|  |  | This project will adopt a cluster-randomized controlled group design to examine the effectiveness of the MVgPA.  **Data collection procedures**  Written consent will be obtained from the participants and their parent or guardian before the data collection. The PA level, PA self-efficacy and interest, and functional exercise capacity of the participants will be measured at the baseline (T0), one week post-intervention (T1) and three months post-intervention (T2) by a trained research assistant (RA2) who is blinded to the group allocation. Information on the sociodemographic and clinical characteristics of the participants will be collected by means of a demographic data sheet via interview and reviewing their record. In addition, the PA organized by the residential care facilities during the study period will also be recorded.  **Outcome measurement**  The PA level of participants (primary outcome) will be assessed in terms of minutes of moderate-to-vigorous PA by using an activity tracker (Fitbit Charge 2), which has demonstrated validity as compared with a research-grade accelerometer, and has been used extensively in western and local studies of adults with ID^9,27,28^. The PA level will be calculated as the average time (minutes) of moderate-to-vigorous PA after five consecutive weekdays of measurement at T0, T1 and T2, as they might go back home during the weekend. The staff of residential care facilities will be asked to remind participants to wear the activity tracker during all waking hours except in wet environment, such as showering, and continue with their usual daily activities during the measurement. The staff of residential care facilities will also be asked to help participants to record the time and reason that the activity tracker is put on and taken off each day.  PA self-efficacy will be measured by using the Chinese version of the self-efficacy scale of the baseline interview questionnaire (BIQ-C)^15^, which includes five items pertaining to the confidence of an individual in performing exercise. The items are rated on a three-point Likert scale (1=not at all sure; 3 = totally sure). The BIQ-C has demonstrated acceptable reliability (Cronbach’s ɑ = 0.75) and construct validity among the Chinese adults with ID^15^.  The functional exercise capacity of the participants will be assessed by conducting 6MWT, which has shown to be reliable and valid when used on adults with ID^29^. The participants will be asked to walk as quickly as possible on a flat, hard surface along a straight path in a period of 6 min.  The interest in performing PA and satisfaction level of MVgPA program of participants will be assessed by using a visual analogue scale (VAS), which consists of a 100 mm long line with the left anchor representing “no interest/not satisfied at all” and the right anchor representing “most interested/most satisfied”.  The satisfaction of residential service providers with the MVgPA intervention and their willingness to continue with the program will be measured at T1 by using an author-developed questionnaire. The staff involved in the MVgPA will be asked to rate their satisfaction and willingness on a six-point Likert scale.  **Ethical considerations**  Ethical approval will be sought from the research ethics committee of the study institution. Participants and their parents/guardians will be assured of confidentiality of any data collected, their participation is voluntary and of their right to withdraw from the study at any time without giving a reason, which will not affect their treatment or relationship with their service providers and the university. |
|  | (vii) | Results analysis |
|  |  | Appropriate descriptive statistics will be used to summarize and present the study data. Skewed continuous variables will be appropriately transformed before analysis. By considering the potential design effect of the randomization conducted in cluster level instead of individual participants, the outcome analysis will be performed on the basis of a three-level mixed effects model accounting for inter-correlation among individuals within the same cluster as well as intra-correlation over time within an individual and variations between individuals. This type of model can account for intra-correlated clustered and repeated measures data and produce unbiased estimates even in the presence of missing data, provided that the data are missing at random. Mixed-effects model will be used to compare the differential changes in each outcome variables (PA level, PA self-efficacy and interest, and exercise capacity) across time (T0, T1, T2) between the two groups. Positive significant group-by-T1 and group-by-T2 interaction-terms in the mixed-effects models indicate significantly greater increment of intervention group in the underlying outcome than the control group at the respective time-points with respect to T0.  The primary analysis of the outcome comparisons will be conducted on the basis of intention-to-treat principle, That means all the randomized participants will be included in the analyses and analyzed according to the groups they are originally allocated. Since all the baseline data, including outcomes, will be collected from all participants before randomization, so all the participants should have at least one measurement (observation) for each outcome and can be included in the mixed-effects model for outcome comparison. For participants who could not follow the intervention owing to the change in medical conditions or other reasons, their data will be continued to be collected at the follow-up time points. If there are considerable missing follow-up data, say >10%, sensitivity analysis will also be conducted to assess the robustness of the primary analysis results. In this connection, multiple imputation method will be used to impute missing data, using all available baseline characteristics as covariates. Predictive mean matching approach^30^ which relies less on the parametric assumptions of the imputation models will be used. Furthermore, a post hoc subgroup analysis will be performed to examine the effects of the intervention between those with and those without Down syndrome if a considerable proportion of the participants have such syndrome. Cohen’s d effect sizes will be computed for the outcomes to demonstrate the effectiveness of the programme. All statistical analyses will be conducted using SAS release 9.4 (SAS Institute Inc, Cary, NC). All statistical tests involved will be two-sided with level of significance set at 0.05. |
